#### Change in alcohol approach avoidance imaging assessment (secondary)

While undergoing fMRI, participants will complete a modified Alcohol Approach Avoidance assessment. In this task, 20 alcohol images and 20 neutral images matched for perceptual features are presented in a pseudo-randomized order (i.e., streaks greater than 4 are eliminated), with a total of 160 trials over 2 blocks. Images are distinct from those used in the behavioral and training tasks. As the goal is to assess the neural correlates of approach bias, the pictures will be pushed and pulled equally often (50% alcohol / 50% neutral). Pushing and pulling cues are accompanied by the visual feedback of the cue zooming out and in, respectively. Participants are told to “make the picture disappear as soon as possible,” and to pull or push in response to a green or blue border, respectively. They have 2.5 s to respond to a picture before auto-forwarding and the trial discounted. Intertrial intervals are 0.5–10 s distributed at random (jittered). The task outcome is blood oxygen level dependent (BOLD) response to a primary contrast comparing alcohol to neutral beverage for push versus pull (alcohol pull – alcohol push > neutral pull – neutral push).

### Intervention

Veterans will be randomized to an AAT or Sham Condition. In these paradigms, participants are first shown a fixation cross, followed by an image (alcohol or neutral beverage) with a colored border surrounding it. They then use a joystick to respond to the color of the border surrounding the stimulus image (i.e., pull for green, push for blue). To experimentally manipulate automatic action tendencies, in AAT a contingency is set between alcohol stimuli (i.e., alcoholic beverage images) and avoidance behaviors (i.e., arm extension or push) in the active AAT condition. Thus, in the active condition, the majority of alcohol images (92%) are presented with a blue border that indicates an instruction to push (i.e., avoid). Participants randomized to the Sham condition will complete a computer-delivered program that is similar to AAT, and matched for number of sessions, but without a contingency between instruction type and pictures (i.e., 50% pull). The AAT and Sham paradigms consist of 192 trials, including 16 alcohol images (4 of each image type: beer, wine, spirits, and mixed beverages) and 16 neutral images, where each image repeats 6 times. Participants will be instructed to complete the AAT or Sham tasks twice weekly, starting from their first week in outpatient treatment, for six weeks. The programs will be completed using a joystick either in an exam room on site or remotely. Participants choosing to complete the intervention remotely will be provided a joystick.

### Monitoring

A data monitor will oversee the present study. The main responsibilities of the data monitor will include reviewing the protocol prior to recruiting, meeting annually with the research team, and annual monitoring of study activities and oversight of any adverse events for safety purposes. The local San Diego Healthcare System Institutional Review Board will conduct an annual audit of the present study which includes a review of enrollment, consent, eligibility, adherence to trial procedures and policies to protect participant confidentiality, and reporting of adverse events.

The safety monitor will oversee the study and report any issues regarding safety or threats to data integrity to the IRB. In the present study, all Serious Adverse Events (SAEs) (i.e., any fatal event, immediately life-threatening event, permanently or substantially disabling event, or event requiring or prolonging inpatient hospitalization) will require immediate review and will be reported to the safety monitor regardless of any judgement of their relatedness to the study. SAEs will be reported to the local IRB within 24 hours of the SAE. A summary of Non-Serious Adverse Events will be provided to the safety monitor annually. Additionally, a summary of participant retention and reasons for participant dropout by experimental condition will be provided (by KH) to the safety monitor.

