**Methods:**

One hundred thirty-six Veterans currently receiving outpatient treatment for AUD will be recruited for this randomized controlled trial with parallel group assignment. Participants will be randomized to either 6 weeks of AAT (n = 68) or Sham (n = 68) training in conjunction with usual care. Assessments will occur at baseline and 6 weeks, 3 months, and 6 months post-baseline. Primary outcome variables will include functional consequences of drinking. Secondary outcome variables will include alcohol consumption, and behavioral indicators of alcohol approach bias. A subset of participants (n = 51) will also complete functional magnetic resonance imaging (fMRI) to assess neural response during an alcohol approach bias assessment.

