### Eligibility criteria

Participants must be Veterans between 18 and 65 years of age (inclusive of all sexes); have a primary diagnosis of AUD (i.e., meet *Diagnostic and Statistical Manual of Mental Disorders, Fifth Edition* (DSM-5) criteria for AUD); have no more than 90 days abstinence from alcohol prior to study participation; and must have 4-week stability if taking psychotropic medications at the time of enrollment. Participants will be excluded if they have a lifetime history of psychotic or bipolar disorder; neurodegenerative or neurodevelopmental disorders; history of moderate or severe traumatic brain injury or other known neurological conditions; sensory deficits that would preclude completing behavioral tasks; suicidal or homicidal ideation within the past month necessitating urgent higher level care; concurrent individual psychotherapy or other treatment outside of standard clinical programming; conditions unsafe for completing MRI scanning for those completing the scanning component only (e.g., non-scan safe metal in body).

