### Procedure

Data collection is planned to take place between February 2023 and May 2026. Eligible participants will be enrolled in concert with clinical treatment initiation. Following a brief telephone screening, participants will complete a baseline visit that includes written informed consent, structured clinical interviews, and self-report questionnaires. At the time of consent, participants will be informed that they may refuse to participate or discontinue at any time and any participants wishing to withdraw will be given referrals for VA mental health services. If a participant expresses significant distress or discomfort during any procedures, the principal investigator will be notified and provide appropriate referrals or other clinical action. If eligibility is confirmed, participants will complete a second visit that includes the behavioral task (Alcohol Approach Avoidance Assessment). If participants are eligible to undergo fMRI scanning, they will complete the modified Alcohol Approach Avoidance Assessment while in the scanner. Training will be scheduled upon completion of visit 2. Participants will be scheduled to complete visits twice weekly for six weeks but will have up to 10 weeks to complete the 12 training sessions in the event of rescheduling. Immediately following the final training session, participants will complete two post treatment visits that mirror the first two assessment visits. Three months and six months after baseline, a research team member will administer the TLFB and assess treatment change. At these final two treatment follow-up appointments, participants will complete self-report questionnaires. See Table 1 for an outline of measures included in each appointment.

**Table 1 Tab1:** Measures by Visit

	Enrollment		Post-allocation			
Timepoint	Screening		Visit 2	Post	3-mo	6-mo

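### The closed SAE list has no item for suicide attempts or other important medical events that are neither immediately life-threatening, disabling nor admitted, so their only scheduled route to the safety monitor is an annual summary.

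*Protocol article*

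**What the plan says.** The Monitoring section of the protocol article sets up two reporting tracks.

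- **Serious events.** The definition is introduced by i.e. and so reads as complete: "any fatal event, immediately life-threatening event, permanently or substantially disabling event, or event requiring or prolonging inpatient hospitalization". These events "will require immediate review and will be reported to the safety monitor regardless of any judgement of their relatedness to the study", and "SAEs will be reported to the local IRB within 24 hours of the SAE".
- **Everything else.** "A summary of Non-Serious Adverse Events will be provided to the safety monitor annually". The data monitor's role is likewise yearly: "annual monitoring of study activities and oversight of any adverse events for safety purposes".

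Three other places bear on the point.

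- Eligibility criteria excludes people with "suicidal or homicidal ideation within the past month necessitating urgent higher level care". Lesser or older ideation does not bar entry.
- Eligibility evaluation and Table 1 place the C-SSRS at baseline and at the post-training visit, with none marked at 3 or 6 months.
- On duration, the Abstract states "Assessments will occur at baseline and 6 weeks, 3 months, and 6 months post-baseline". The Procedure section says that participants "will have up to 10 weeks to complete the 12 training sessions in the event of rescheduling".

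**The concern.** The list has no category for important medical events that fall short of its four criteria. In outpatients with alcohol use disorder and psychiatric comorbidity, several relevant harms can fall there: a suicide attempt without lasting injury, or an overdose, withdrawal seizure or acute intoxication managed in an emergency department and followed by discharge. Suicidal ideation first recorded after training that calls for urgent escalation of care, but not for inpatient admission, has the same problem.

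Under the rule as written, neither the immediate review nor the 24-hour IRB report applies to these events. What is at stake is how soon the person charged with safety oversight learns of them. A yearly summary is long compared with 6 to 10 weeks of training and 6 months of participation.

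**Working it through.** The plan gives no figure to reproduce. There are two checks: which track an event falls on, and how late the yearly summary is.

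**1. Classification.** The listed criteria, applied to a suicide attempt treated in an emergency department and discharged without lasting injury:

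- Fatal: no.
- Immediately life-threatening: depends on the case and on judgement.
- Permanently or substantially disabling: no.
- Inpatient admission required or prolonged: no.

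If the second answer is also no, the event is non-serious. The same holds for an overdose, withdrawal seizure or intoxication with the same course. The only scheduled route to the safety monitor is then the yearly summary.

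**2. Delay.** Inputs from the article: summary interval 12 months; participation 6 months from baseline; training 6 weeks, at most 10 weeks (about 1.38 and 2.3 months). Two assumptions are needed, because the article gives neither event timing nor summary dates: the wait W to the next summary is uniform on 0 to 12 months, and event timing varies as in the table.

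For an event at month t, the summary comes after participation ends if W > 6 − t. Averaged over event times:

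P = 1 − (mean remaining participation in months) / 12

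| Event timing | Mean remaining (months) | P(summary after participation ends) |
|---|---|---|
| Even over 0 to 6 months | 3 | 1 − 3/12 = 75% |
| Within 6 weeks of training | 6 − 0.69 = 5.31 | 1 − 5.31/12 = 56% |
| Within 10 weeks of training | 6 − 1.15 = 4.85 | 1 − 4.85/12 = 60% |
| Found at a post-training visit at 6 weeks | 6 − 1.38 = 4.62 | 1 − 4.62/12 = 62% |
| Found at a post-training visit at 10 weeks | 6 − 2.3 = 3.7 | 1 − 3.7/12 = 69% |
| In follow-up, 6 weeks to 6 months | (6 − 1.38)/2 = 2.31 | 1 − 2.31/12 = 81% |
| Day 0 (limiting case) | 6 | 1 − 6/12 = 50% |

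A simulation with one million draws per row agreed with these values.

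For an event spread evenly over T weeks of training, the chance that the summary arrives before that participant's training ends is (T/2)/52:

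- T = 6: 3/52 = 5.8%, so it comes too late in 94%.
- T = 10: 5/52 = 9.6%, so it comes too late in 90%.

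The average wait is 12/2 = 6 months and the longest is 12 months.

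**The case against.** The strongest reply is that a journal article condenses the protocol, and that detailed seriousness categories or steps for suicidality may sit in the full document. That would answer a complaint about silence. Here the article states the definition as complete, names both tracks and gives their timing; the point concerns that stated rule.

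A second reply is that other routes exist. The safety monitor is to report any safety issue to the IRB, study staff administer the C-SSRS after training, and the principal investigator is told of significant distress during procedures and can act clinically. This stands in part: nothing says that the yearly summary is the only possible channel. But none of these routes has a trigger or deadline for the events in question. Distress during a study procedure does not cover an attempt at home between visits, and the monitor can act only on what is sent.

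A third reply is that the delay figures follow from any yearly summary combined with short participation and do not count misclassified events. That is correct. They measure delay, not frequency. For events during training the 56% to 60% is only a modest majority. Ideation first found at the post-training visit could not reach the monitor before training ends under any definition.

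Four stronger readings might be inferred, and the article does not support them:

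- **Every attempt without admission is non-serious.** Immediate threat to life and disability are separate criteria, so an attempt meeting either is already an SAE without admission.
- **The trial screens for all these events.** Among them, the C-SSRS covers suicidality only. The sections cited here show no screening for overdose, withdrawal seizure or emergency visits.
- **The entry exclusion contradicts the reporting rule.** An entry rule and a reporting rule need not match, and ideation leading to admission is already an SAE.
- **The SAE count will be too low by a known amount.** The article gives no event rate, and the shortfall could be zero.

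**Conclusion.** The point holds within a narrow class: suicide attempts and other important medical events that are neither immediately life-threatening, disabling nor admitted. The stated rule makes them non-serious and schedules them for a yearly summary, which comes after the participant has finished in about 75% of cases. That figure assumes events spread evenly over 6 months and a summary date unrelated to the participant's calendar. The other timings tried give 56% to 81%, and the day-0 limit gives 50%. The number of such events cannot be estimated from the article. Randomisation, endpoints, analysis and power are unaffected; the matter is timely safety oversight in a comorbid sample, and the change is worth making because it is small.

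**What to change.** Two sentences in the Monitoring section would close the gap:

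- Add to the events sent immediately to the safety monitor: other important medical events, including any suicide attempt and any overdose, withdrawal seizure or intoxication needing emergency care.
- Send newly recorded post-training suicidal ideation that needs urgent escalation of care by the same route.

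Leave other non-serious events in the yearly summary.

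This changes reporting only, not clinical management, and needs no new assessments or staff. The cost is some more expedited reports and a higher reported SAE count.

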### Allocation

Randomization will occur during the second visit after eligibility criteria have been confirmed. Randomization sequences will be generated by the study quantitative psychologist, who is not involved in recruitment or data collection, using a computer-generated randomization sequence, using R (*Base* package*)* [50] and administered through RedCAPs randomization function. Randomization will occur without the ability to predict a participant’s allocation before randomizing. Randomization will be blocked (block size = 4 participants; 34 blocks total) and stratified by age category (2 strata: < 40 vs. > = 40 years old) given that age is known predictor of AAT response [31]. The study design will be double-blind, i.e., the participant, assessor, and PIs will be masked to the treatment condition for the duration of the trial with no planned unblinding. Within each stratum, participants will be divided into four groups, i.e., 2 treatment conditions (AAT vs. Sham) X 2 image set orders for Pre and Post Assessment AAT (AB vs. BA), with an allocation ratio of 1:1:1:1. Each computer program corresponding to each of the 4 conditions will be blinded such that the coordinator will not know the nature of the program. Assessors will not deliver the intervention. The patient and assessor will each rate their prediction regarding the patient’s assigned treatment condition after each assessment to check the success of blinding.

### Procedure

Data collection is planned to take place between February 2023 and May 2026. Eligible participants will be enrolled in concert with clinical treatment initiation. Following a brief telephone screening, participants will complete a baseline visit that includes written informed consent, structured clinical interviews, and self-report questionnaires. At the time of consent, participants will be informed that they may refuse to participate or discontinue at any time and any participants wishing to withdraw will be given referrals for VA mental health services. If a participant expresses significant distress or discomfort during any procedures, the principal investigator will be notified and provide appropriate referrals or other clinical action. If eligibility is confirmed, participants will complete a second visit that includes the behavioral task (Alcohol Approach Avoidance Assessment). If participants are eligible to undergo fMRI scanning, they will complete the modified Alcohol Approach Avoidance Assessment while in the scanner. Training will be scheduled upon completion of visit 2. Participants will be scheduled to complete visits twice weekly for six weeks but will have up to 10 weeks to complete the 12 training sessions in the event of rescheduling. Immediately following the final training session, participants will complete two post treatment visits that mirror the first two assessment visits. Three months and six months after baseline, a research team member will administer the TLFB and assess treatment change. At these final two treatment follow-up appointments, participants will complete self-report questionnaires. See Table 1 for an outline of measures included in each appointment.

**Table 1 Tab1:** Measures by Visit

	Enrollment		Post-allocation			
Timepoint	Screening		Visit 2	Post	3-mo	6-mo

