### Outcomes

#### AUD-related disability (primary)

The Drinker Inventory of Consequences (DrInC) assesses alcohol-related adverse functional consequences across physical (e.g., harmed physical health), interpersonal (e.g., loss of relationships), role responsibilities (e.g., missed work), psychological (e.g., loss of hobbies), and impulse control-related problems (e.g., legal problems); the first administration establishes lifetime consequences (DrINC-2 L) and a modified version of the DrInC-2R will be used to assess past 30-day consequences, and subsequent administrations assesses past 30-day consequences [48].

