## Outcomes and statistical methods

### Primary and secondary clinical outcomes

To evaluate whether AAT significantly improves clinical outcomes relative to Sham, a mixed effects model repeated measures (MMRM) model will be used. The dependent variable in the MMRM model is change from baseline in AUD-related disability (DrInC) at each post-baseline visit (post visit, 3 and 6 mo. follow-up). Predictors in the model will include treatment condition (AAT, Sham), visit (immediately post-training, 3 and 6 mo.), condition by visit interaction term, and baseline DrInC. The primary end point is the post-training visit. The same analytic approach will be applied to the secondary outcome (PDHD). We will model the distribution of percent days heavy drinking to ensure appropriate analysis. All subjects randomized will be included in the intent-to-treat analysis. Depending on the type of missing data, the appropriate statistical approach (e.g., multiple imputation) will be determined. Sensitivity analyses will be used to explore the impact of missing data.

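### The primary endpoint visit is set at 6 weeks post-baseline in the abstract but at the end of training in the methods, so its timing depends on session completion

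*Protocol article*

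**What the plan says.** The article times the first follow-up in two ways.

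- Abstract, Methods: "Assessments will occur at baseline and 6 weeks, 3 months, and 6 months post-baseline". This is a calendar time counted from baseline.
- Procedure: "Immediately following the final training session, participants will complete two post treatment visits that mirror the first two assessment visits". This is an event, the end of training. The same section says "Participants will be scheduled to complete visits twice weekly for six weeks but will have up to 10 weeks to complete the 12 training sessions", the extra time being for rescheduling. It also says "Training will be scheduled upon completion of visit 2"; under Allocation, visit 2 is also where randomisation takes place. The 3- and 6-month follow-ups are counted from baseline.

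Primary and secondary clinical outcomes then states: "The primary end point is the post-training visit". It gives no target week and no window. The MMRM takes visit as a factor with three levels (post-training, 3 months, 6 months). On the analysis population it says: "All subjects randomized will be included in the intent-to-treat analysis".

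For the primary outcome (DrInC), after the first administration, "subsequent administrations assesses past 30-day consequences". The TLFB, which supplies the secondary outcome PDHD, covers the interval since the previous interview.

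**The concern.** Of the three post-baseline visits, only the primary one is tied to finishing training. Three things follow.

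1. The elapsed time at the primary visit depends on how quickly the sessions are completed. People who reschedule often may differ in their drinking from those who do not, and the model places both under one visit label.
2. The only trigger given is the final session. Read literally, someone who stops training never reaches it, and the primary outcome could go missing because of non-adherence in an analysis meant to include everyone randomised. A sensitivity analysis for missing data cannot recover an assessment that was never scheduled.
3. A late post-training visit moves towards the fixed 3-month visit, so the two 30-day DrInC windows can share days. The period covered by the 3-month TLFB also shrinks.

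**Working it through.** The plan has no calculated figure on this point to reproduce. The sample size of 136 does not enter, so the check is day arithmetic on the stated schedule.

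**Inputs from the article**
- Training length: 6 weeks planned, 10 weeks at most (Procedure).
- Training starts after visit 2 (Procedure).
- 3-month visit counted from baseline (Procedure), taken as day 91.
- DrInC recall after baseline: 30 days (Outcomes).
- TLFB after baseline: time since the last interview (Outcomes).

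**Assumptions**
- The interval from the baseline visit to the start of training is not given, so 0, 1 and 2 weeks are shown.
- The post-training DrInC is taken on the day of the last session. There are two post-treatment visits, so any delay would move it later.

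**Formulas**
- Post-visit day P = 7 × (weeks from baseline to training start + weeks of training).
- Days to the 3-month visit, which is also the length of the 3-month TLFB period = 91 − P.
- DrInC overlap = max(0, 30 − (91 − P)). Overlap begins once P exceeds 61.

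| Gap to training start (weeks, assumed) | Training (weeks) | P (day) | Days to 3-month visit | DrInC overlap (of 30 days) |
|---|---|---|---|---|
| 0 | 6 | 42 | 49 | 0 |
| 0 | 8 | 56 | 35 | 0 |
| 0 | 10 | 70 | 21 | 9 |
| 1 | 6 | 49 | 42 | 0 |
| 1 | 8 | 63 | 28 | 2 |
| 1 | 10 | 77 | 14 | 16 |
| 2 | 6 | 56 | 35 | 0 |
| 2 | 8 | 70 | 21 | 9 |
| 2 | 10 | 84 | 7 | 23 |

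**Reading the table**
- The abstract's 6 weeks (day 42) is met only with six weeks of training and no gap. Every other row falls later.
- Among completers, the spread from training length alone is 10 − 6 = 4 weeks, which is 4/6 = 67% of the planned training period.
- Overlap of the DrInC windows is confined to slow completers. It is zero on the six-week schedule for all three gaps.
- TLFB periods never overlap, because each starts where the previous one ended. The 3-month period varies from 49 days to 21 with no gap, and down to 7 with a 2-week gap.

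**The case against.** The strongest reply is that a journal article describes the ordinary path and leaves visit windows and the handling of early stoppers to the full protocol. The final session could also mean the last one attended, or the 10-week limit could close the training period and prompt the visit. The article does commit to analysing everyone randomised, to a missing-data method and to sensitivity analyses. An end-of-training endpoint is also a legitimate choice. This stands in part: the article does not say that early stoppers go unassessed, and that part of the point rests partly on silence. It does not remove the conflict between 6 weeks and the end of training, which concerns the single primary time point. Nor does it change the fact that the one stated rule fits poorly with the intent-to-treat commitment.

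A reader might infer more than the article supports:

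- **That 27 to 34 participants would lack a primary assessment.** These are 20% and 25% of 136 (27.2 and 34), but the percentages are total attrition. People lost to follow-up would be missing at a fixed date too. The number who stop training but could still be assessed is not stated and cannot be derived.
- **That the treatment comparison is biased.** The arms are matched for number of sessions and participants are masked. Different timing by arm would need different adherence by arm, which nothing in the article shows.
- **That the post-training and 3-month outcomes largely cover the same days.** The 23 of 30 days needs the full 10 weeks plus an assumed 2-week gap. The Intervention section has training begin in the first week of outpatient treatment, which suggests a shorter gap. Only DrInC is affected, and overlap with a later visit does not by itself bias the primary contrast.

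**Conclusion.** The point holds as an inconsistency about the primary time point, together with an anchor that depends on completing training. The abstract and the Procedure section cannot both be followed once training runs past six weeks or starts after baseline. For completers the visit falls about 6 to 10 weeks after training starts, later when counted from baseline.

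The consequences supported by the article are mixed elapsed times within one model visit, possibly avoidable missing primary data, a 3-month TLFB period of varying length and, for those using all 10 weeks, DrInC overlap of about 9 days with no gap (16 or 23 days under an assumed 1- or 2-week gap). The overlap figures rest on day 91 for the 3-month visit and on DrInC being taken at the last session. Neither the number of participants affected nor any loss of power can be calculated from what is stated.

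**What to change.** Reconcile the abstract, the Procedure section and the primary-outcome analysis section so that they give the same primary time point. Schedule the primary DrInC and TLFB assessment at one stated time from randomisation, with a window, for every randomised participant, whatever number of sessions was completed and whether or not training has stopped. If the window closes by day 61 from baseline, the DrInC overlap with the 3-month visit also disappears. The training allowance need not change, and the behavioural task and fMRI visit may stay tied to the last session if that is wanted.

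The cost is protocol wording and scheduling, with one real downside. Some slow completers would be assessed before their last session, or would need a short separate questionnaire and TLFB contact, a small added burden in a population whose burden the article is trying to limit.
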